### Study population and setting

#### PrEP users

PtC utilises a prospective cohort design that recruits up to 1800 adolescents and young people, specifically adolescent girls and young women (15–29 years) including pregnant and breastfeeding women, young male key populations including gay and other men who have sex with men (15–29 years), and their collective male partners (> 15 years). In order to participate, the participant must belong to one of three population groups as described, be HIV negative at baseline, be resident in or have frequent presence within the study area, and able to provide voluntary informed consent to participate in the study. The study aims to recruit at least 100 pregnant and breastfeeding participants. Use of a particular PrEP product may be further restricted by clinical criteria, which differs by product (see Table 2).

**Table 2 Tab2:** Exclusion criteria by product

	Tenofovir disoproxil and emtricitabine (Oral PrEP)	Dapivirine (Vaginal Ring)	Cabotegravir long-acting (Injectable PrEP)
	Unknown or positive HIV-1 status is an exclusion criterion for all PrEP products		
Clinical criteria	• Weight < 35 kg • Previous hypersensitivity to any components.	• < 18 years old • Pregnancy • Hypersensitivity to any of the excipients (*Dimeticone and/or silicone elastomer)*	• Inflammatory skin conditions that compromise the safety of intramuscular (IM) injections • Weight < 35 kg • Previous hypersensitivity reaction to Cabotegravir
Contra-indicated concomitant medications	Co-administration with other Tenofovir-containing, emtricitabine-containing, or lamivudine containing products	None	(1) Anticonvulsants: Carbamazepine, oxcarbazepine, phenobarbital, phenytoin (2) Antimycobacterials: Rifampicin, rifapentine

Pregnant participants are included in the study and able to select oral or injectable PrEP options, following comprehensive risk-benefit counselling. The safety of oral PrEP in pregnancy is well-established and recent data demonstrates that CAB-LA is well tolerated during pregnancy and postpartum, has a similar pharmacokinetic profile in nonpregnant and pregnant women, and has shown no significant increases in adverse pregnancy or birth outcomes, including neural tube defects [17, 19]. The DapiRing is currently not approved for use in pregnant and breastfeeding women in South Africa but is expected to approved soon with recent research demonstrating safety for use in pregnancy [20]. 

Participants may be naïve to PrEP use, using PrEP through government PrEP services, or they may be recruited from an existing and affiliated large-scale PrEP programme in the study area (“FASTPrEP”), which operates four mobile clinics, a PrEP depot site, as well as from all public health clinic facilities in the study area [21]. FASTPrEP is a novel demonstration project designed to introduce, scale up, and evaluate current (oral PrEP and DapiRing) provision through differentiated models of service delivery that integrates PrEP into a comprehensive SRH package [21]. Enrolment on PtC for non-FASTPrEP participants necessitates simultaneous co-enrolment on FASTPrEP. PtC is promoted at all existing FASTPrEP sites and through its existing social media platforms.

*Sample size calculation*: With 900 participants who start CAB-LA, the study will have > 85% power to detect an 8% or greater difference in PrEP persistence at 7 months comparing oral PrEP users to injectable PrEP or injectable vs. DapiRing selectors using a simple chi-square test. We conducted a sensitivity analysis to estimate the power with different levels of sample size at 95% confidence interval. If a lower sample size were reached, we would have > 80% power to detect a 11% difference or more with 700 participants in CAB-LA vs. 200 in oral PrEP. Study enrolment will cease once a minimum of 900 participants have self-selected to initiate on CAB-LA at baseline, irrespective of the number of oral PrEP and DapiRing users at that time point.

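### The >85% power for an 8-point difference is attributed to the 900 CAB-LA starters alone; with no comparator size stated or secured, the design does not guarantee it

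*Protocol article*

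**What the plan says.** All the relevant text is in the protocol article under PrEP users.

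- Headline claim: "With 900 participants who start CAB-LA, the study will have > 85% power", specified as "power to detect an 8% or greater difference in PrEP persistence at 7 months comparing oral PrEP users to injectable PrEP". The contrasts are described in full as "comparing oral PrEP users to injectable PrEP or injectable vs. DapiRing selectors using a simple chi-square test". No number of oral or ring users and no assumed persistence rate goes with it.
- A sensitivity analysis was run to "estimate the power with different levels of sample size at 95% confidence interval". The one result reported is more than 80% power for an 11% difference with 700 on CAB-LA and 200 on oral PrEP. This is the only comparator size in the article.
- Enrolment ends once at least 900 participants have started CAB-LA, "irrespective of the number of oral PrEP and DapiRing users at that time point".
- Overall size: "PtC utilises a prospective cohort design that recruits up to 1800 adolescents and young people".

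Elsewhere, Aims and objectives states the hypothesis that persistence is greater on CAB-LA than on oral PrEP and/or the ring. Table 1 makes the comparison of 7-month persistence across products primary aim 1.1. Statistical analysis confirms a chi-square comparison of the proportions persisting among those who started each product.

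**The concern.** The power statement fixes one arm of a two-arm comparison and leaves the other open. With 900 on CAB-LA, the smaller group dominates the standard error, and that group is oral or ring users. Participants choose their product, so its size is unknown in advance, and the stopping rule sets no minimum for it.

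Small comparator groups are foreseeable from the article itself. The Background reports a theoretical preference for long-acting products in several of the target groups. The ring is limited to women who are not pregnant or breastfeeding (Aims and objectives) and are at least 18 (Table 2), while the cohort also takes in males, 15–17-year-olds and at least 100 pregnant or breastfeeding participants. Yet the ring comparison is given the same power as the oral one.

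At stake is how primary aim 1.1 is read. A non-significant product comparison would be judged against a published figure above 85% when its actual power might be little better than even, and could be taken as evidence that persistence is equal.

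**Working it through.** **Inputs from the article:** n₁ = 900 on CAB-LA; difference 8%, read as absolute percentage points; CAB-LA higher, as hypothesised; chi-square test; cap of 1800, so at most 1800 − 900 = 900 participants on other products.

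**Assumptions, not in the article:** two-sided 5% (alpha is not stated; the chi-square test and 95% level point to it); comparator persistence p₂ of 30–60%, with p₁ = p₂ + 0.08. No loss to follow-up or confounder adjustment is included.

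**Formula** (pooled-variance normal approximation to the chi-square test):

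Power = Φ{ [Δ − 1.96·√(p̄(1−p̄)(1/n₁+1/n₂))] / √(p₁(1−p₁)/n₁ + p₂(1−p₂)/n₂) }, where p̄ = (n₁p₁+n₂p₂)/(n₁+n₂).

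**Step 1: the plan's own figures.** The >85% cannot be reproduced because n₂ and p₂ are missing. The companion figure can be checked: 700 vs 200 at 11 points gives 78.6% at worst (p₂ about 43%) and more than 80% for p₂ up to about 33% or from about 53%. That agrees with the stated >80% to within about 1.4 points, so it is no error and plays no part in this point.

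**Step 2: worked cases at p₂ = 45%, p₁ = 53%.**

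- n₂ = 450: p̄ = 0.5033; standard errors 0.02887 (null) and 0.02875 (alternative). (0.08 − 1.96×0.02887)/0.02875 = 0.81; power 79.2%.
- n₂ = 200: p̄ = 0.5155; standard errors 0.03907 and 0.03891. (0.08 − 1.96×0.03907)/0.03891 = 0.09; power 53.5%.
- n₂ = 573: p̄ = 0.4989; standard errors 0.02672 and 0.02662. (0.08 − 1.96×0.02672)/0.02662 = 1.04; power 85.0%.

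**Step 3: power across assumed comparator persistence.**

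| Comparator n₂ | p₂ = 30% | p₂ = 45% | p₂ = 60% |
|---|---|---|---|
| 200 | 56.8% | 53.5% | 58.0% |
| 225 | 61.1% | 57.5% | 61.9% |
| 450 | 83.1% | 79.2% | 82.6% |
| 573 | 88.5% | 85.0% | 87.8% |
| 900 | 94.8% | 92.5% | 94.3% |

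The 450 row is the full cap split equally between oral and ring. The 225 row is an illustration: 80% choose CAB-LA (900/0.80 − 900 = 225) and all the rest choose one product. The 200 row uses the oral number from the article's low-uptake scenario.

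**Step 4: comparator size needed for 85%.** 486 (p₂ = 30%), 561 (40%), 573 (45%, the worst case), 566 (50%), 499 (60%).

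**Step 5: what the cap allows.** For one comparison, 573 comparators are enough at any baseline, and 900 − 573 = 327 places remain. For two comparisons at 450 each, power is below 85% for p₂ from about 27% to about 64%, and reaches 85% at about 26% or lower, or about 65% or higher.

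**Step 6: detectable difference at 50% persistence and 85% power.** From (1.960 + 1.036)·√(0.25/900 + 0.25/n₂): 8.65 points for 450, 11.7 for 200, 15.8 for 100. Searching with the Step 2 formula gives 8.6, 11.6 and 15.4.

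**The case against.** The strongest reply is that the claim can be true. The two contrasts are joined by *or*, and the hypothesis is worded and/or. On that reading only one comparison needs the power, and 900 vs 573 delivers it at any baseline within the cap. A reader might go further and infer that >85% cannot hold for both products within 1800, since two comparators would need 2×486 = 972 to 2×573 = 1146 participants against 900 available. The article does not support that as a general statement: it depends on reading *or* as both, on mid-range persistence that the article does not give, and on equal persistence in the two groups.

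A reader might also infer that the stopping rule destroys the power. It does not; it leaves the power unsecured. If enough participants choose one comparator, the claim is met. The article is open that oral and ring numbers are free, and it gives a low-uptake scenario with a larger detectable difference. The 200 oral users belong to that scenario and do not contradict the 8% claim.

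The test could be one-sided. At 5% one-sided, 450 per comparator gives at least 87%, but 200 gives only about 66–70%, so the dependence on uptake remains.

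Finally, an article condenses, and the full protocol may hold the assumed rates and a fuller sensitivity table. That is fair as to missing detail. It does not answer the conflict within the paragraph: power is promised on the CAB-LA count alone, while the rule that follows leaves the other determinant of power without a floor.

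**Conclusion.** The point holds in this form: the >85% is stated as a property of the design, but it is conditional on a comparator size that is neither stated nor secured. Following the enrolment rule as written can leave a primary comparison far below the published figure. Over an assumed comparator persistence of 30–60% (two-sided 5%, absolute 8 points), power is 79–83% with 450 comparators, about 57–62% with 225 and 53.5–58% with 200. The size of the shortfall rests on those assumptions; outside mid-range persistence it shrinks or disappears for groups of about 450. It is not shown that the claim is unattainable, nor that the 11-point figure is wrong.

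**What to change.** Replace the unconditional sentence with a short table of power, or of detectable difference, by comparator size and assumed persistence, and state the persistence rates, alpha and sidedness used. At 50% persistence and 85% power the entries would be about 8.6 points for 450 comparators, 11.6–11.7 for 200 and 15.4–15.8 for 100.

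Say that power for the oral and ring comparisons is conditional on uptake under the existing stopping rule. Commit to reporting product differences with confidence intervals, and to not reading a non-significant result against a small group as equal persistence. A stated group size below which a comparison is descriptive only would help.

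No participants, visits or analyses are added. The cost is a few lines of text and a less favourable power statement.

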#### PrEP providers and their role

PrEP delivery in SA is nurse-driven and delivered, with PrEP dispensing allowable for any Nurse-Initiated Management of Antiretrovirals (NIMART) qualified practitioner. PtC is delivered by a team of PrEP providers that include NIMART qualified nurses, HIV counsellors, and peer navigators (trained youth aged 18–29 from the study area) [21]. At both the mobile and clinic setting, potential participants are welcomed by peer navigators who provide general HIV health promotion talks and information about the study. Interested participants are seen by the HIV counsellor, following registration and consent procedures, who conduct HIV testing and PrEP choice counselling (average time 30 min) for all HIV negative participants.

Participants are then referred for a nurse-led clinical assessment for eligibility to use the PrEP product of choice and PrEP administration. Administration involves injection of CAB-LA, provision (and insertion if requested) of the DapiRing, or provision of a 30-day oral PrEP supply. All participants are required to return at one month post PrEP initiation to assess safety and interest in continuation on the product and receive their second loading CAB-LA injection or a three-month supply of oral PrEP or DapiRing. All members of the team are trained in adolescent and gender friendly health care and good clinical practice.

#### PrEP choice counselling

 The PrEP choice counselling script was co-created through two formative workshops, one with PrEP-experienced health care providers and administrators (*n* = 25) and one with members of the FASTPrEP youth reference committee (*n* = 10). Feedback from these workshops, alongside choice counselling literature and South African national recommendations for CAB-LA counselling, was used to create the first version of the script, which is delivered using a motivational interviewing approach [22]. The counselling process is monitored through quarterly fidelity checks with opportunity for iterative adjustments based on feedback from the fidelity visits and the counsellors. The aims of the counselling session (which were created during the formative workshops) are firstly, to provide comprehensive information about each PrEP product, and secondly, to empower the PrEP user to contextualise that information within their own lifestyles and sexual practises.

#### Setting

Participants are recruited from the Mitchells Plain-Klipfontein health-sub-district in Cape Town, South Africa. Demand creation for PrEP is currently ongoing in this district under the FASTPrEP programme, whereby the communities are exposed to PrEP educational materials and encouraged to visit community and public health sites to access SRH services, including PrEP [21]. While the FASTPrEP project operates from several mobile, clinical, and community sites (including schools), this study operates from a single mobile and a single clinic site. These sites were selected based on a record of high numbers of oral PrEP users during the preceding year of FASTPrEP implementation and support from local district health officials. The overall model of differentiated PrEP service delivery is outlined in Table 3.

The mobile setting is a Desmond Tutu Health Foundation run mobile clinic that comprises of trained research staff who follow research-specific protocols with resources afforded to them by the research project budget. The primary aim of this site is SRH services and associated research activities. The government health clinic is a government primary health care facility comprising of government clinical and administrative staff, with support from PtC research staff embedded on-site (including a research assistant, HIV counsellor, and two peer navigators), and which follows national, provincial, and local healthcare delivery guidelines and is limited by the resources available to the state. The primary focus of this clinic is healthcare delivery, including services beyond SRH such as antenatal care, HIV treatment, and a midwife obstetric unit. There are minor differences in clinic flows between the sites which have potential to differentially influence the participant experience of the study, PrEP choice counselling, and PrEP administration.

**Table 3 Tab3:** Differentiated service delivery of PrEP choice

	Oral PrEP	Vaginal PrEP	Injectable PrEP
Where (Service Location)	Mobile clinic Government health clinic		
Who (Service Provider)	NIMART-qualified nurses (with medical officer oversight) Lay counsellors Peer Navigators		
When (Service Frequency)	At initiation – one month supply given After 1 month – 3 month supply given	At initiation – one month supply given After 1 month – 3 month supply given	Initiation doses: At initiation and one month Maintenance doses: Every 8 weeks
What (Service Package)	PrEP Choice counselling HIV testing: self-testing option for courier users. Comprehensive SRH service: STI testing and treatment Pregnancy testing and contraceptive counselling		The same, excluding HIV self-testing option

### Clinical intervention components

PrEP schedules differ by product, as follows:

#### Oral PrEP

Oral PrEP is currently standard of care in SA and this study follows national oral PrEP guidelines with regards to counselling and administration [23, 24]. A notable difference is the promotion of event-driven PrEP for male participants, whereby oral tablets are taken in a 2-1-1 formation (two tablets 2–24 h prior to potential HIV exposure and then continue one tablet daily until two days after the last potential exposure). Event-driven PrEP is not part of national PrEP guidelines but is widely supported and expected to be introduced into updated national guidelines expected in 2025.

#### DapiRing

The DapiRing provides a slow release of Dapivirine, a non-nucleoside reverse transcriptase inhibitor, intra-vaginally for 28 consecutive days [25]. The first ring is inserted by the nurse/clinician with guidance given for future self-removal and self-insertion and ongoing training is provided at replacement visits as required. As DapiRing is becoming part of standard of care in SA, it is available at select demonstration sites outside of this study [25]. 

#### CAB-LA administration

CAB-LA is delivered in a long-acting suspension via an intramuscular injection every eight weeks, as a 3 ml injection containing 600 mg of Cabotegravir [26]. Administration is performed by a NIMART qualified professional nurse trained in antiretroviral drug delivery and in the appropriate injection technique. All sites are equipped with resuscitation equipment and trained in basic life support, with participants required to remain on site for a 10-minute observation period post-injection. A second initiation dose is provided at 1 month. Participants are required to return for that scheduled visit within 28 days in order to continue the schedule. Those that return more than 28 days after the scheduled visit (i.e. >56 days after the first injection) are required to re-start the injection schedule. Thereafter, injections are given every 8 weeks with specific guidelines to support continuation after missed injections (< or > 4 weeks since target injection date) [26]. 

For both oral PrEP and DapiRing, a single month’s supply (one tablet bottle or one ring) is supplied at the initiation visit and the participant is required to return after one month to assess product suitability and sustained use. If the participant selects to continue with this product, they are provided with a three-month supply (three tablet bottles or three DapiRing products). This reduces the overall number of clinic visits required for oral and ring participants compared to injectable PrEP, which necessitates in-person visits at least every 2 months. Oral and ring PrEP users may further opt to receive their next supply via courier. In the courier package, they receive an HIV self-test, instructions on how to do the test and where to send results. Access to subsequent courier deliveries is dependent on disclosure of HIV self-testing results.

Participants are counselled to return for study visits even if they would like to discontinue PrEP such that they can receive support in switching PrEP products or safely discontinuing. PrEP product switches are allowed at any point throughout the 18 month study timeline. Written material on safe discontinuation is provided and a WhatsApp line for PrEP support is available if they are unable to return. An automated reminder is sent by short messenger service (SMS) one week prior to the scheduled visit. Participants that do not return for scheduled visits within 7 days are followed up via phone, message, and home visit (if safety is a concern and permission has been granted). Specific counselling on the duration of CAB-LA in the body post injection and the potential risk of antiretroviral drug resistance developing if HIV infection occurs is included before and after starting CAB-LA.

### Clinical testing and screening

#### HIV testing

 All participants are required to undergo HIV testing prior to commencement with PrEP products to confirm their HIV-negative status. There is a risk that participants initiated on CAB-LA during an acute HIV infection will have a delayed immune response to HIV (suppressing HIV viral replication and thereby reducing the generation of anti-HIV antibodies- this is known as the LEVI syndrome) [27]. This could delay diagnosis and increase the risk of HIV drug resistance. To mitigate this risk, some regulatory bodies have required NAAT HIV testing at baseline and throughout CAB-LA to allow for early detection. The WHO, however, have acknowledged the high cost and resource burden of NAAT testing as well as its lack of regulatory approval as an HIV diagnostic test and recommends continued use of national HIV testing algorithms that rely on 3rd or 4th generation rapid antibody/antigen tests. To investigate this approach, PtC participants undergo HIV testing at each visit with 3rd and 4th generation HIV rapid tests, the results of which guide eligibility for same day PrEP initiation, after additionally confirming the absence of signs or symptoms of acute HIV exposure and/or a recent history of a potential HIV exposure that would indicate the need for post-exposure prophylaxis (PEP). Viral load (NAAT) testing is conducted in the laboratory at baseline, month 1, month 7 (range 5–8 months), and month 17 (range 16–18 months) post-PrEP initiation to validate the rapid results. In the case of a detectable viral load test result post-PrEP initiation, the participant is recalled for further confirmation of the HIV testing results and rapid transition to HIV treatment and care if applicable. This will provide evidence to confirm or refute the superiority of (and thus necessity to use) more expensive and resource-intensive viral load tests for CAB-LA users in this setting. Participants on CAB-LA who seroconvert are invited to take part in an affiliated study investigating salvage treatment options.

#### Additional safety tests

 At study initiation, all CAB-LA selecting participants have blood draws to screen for Hepatitis B (Hepatitis B surface antigen test) and an abridged liver function test (including liver transaminases and total bilirubin) to rule out pre-existing liver pathology. CAB-LA injections are not delayed until these results are available and participants are recalled within a week for clinical review should any laboratory results be of concern. In the case of concerning results, participants are recalled and managed on a case-by-case basis with oversight from the study’s Clinical Management Team. Previous work in this study setting showed that HBV prevalence is very low in young female populations (0.69% overall and 0% in those born after 1995), likely due to high HBV vaccine coverage; however, it may be of concern in older male participants that are also at greater list of other hepatology conditions and greater alcohol use [28]. 

